**8. ANALYSIS**

The method of target trial emulation (3, 4) will be applied to examine the relationship between statin therapy and risk of the outcomes of interest. The patients will be categorized into different age groups (60-74, 75-84, ≥85 years) for analysis. The analysis of those aged between 60-74 years will serve as a benchmark to test the validity of our emulated trial since the effect of statin therapy is well-established in this population (5, 6).

**Main analysis:** Propensity score matching will be employed to emulate the randomization of the eligible person-trials at baseline, where initiators and non-initiators will be matched in a 1:1 ratio within each age group (60–74, 75–84, ≥85 years). The matching factors included the aforementioned covariates and the baseline calendar month. The intention-to-treat (ITT) and per-protocol effects on the prevention of CVDs and all-cause mortality will be estimated in the emulated target trials in the three age groups. The ITT analysis will compare the risk for outcome incidence between statin initiators and non-initiators, as defined by their treatment strategy at baseline. The hazard ratio will be estimated by fitting a pooled logistic model for the outcome incidence, including the indicators of the assigned strategy (statin initiation at baseline), follow-up period (linear and quadratic terms), and the aforementioned covariates at baseline. The per-protocol analysis will compare risks for the outcomes of interest between continuous users and those who never use statins during the follow-up period, where the person-trials will be artificially censored if participants deviate from their assigned strategy unless they develop an indication or contraindication for statin therapy. To adjust for selection bias resulting from the artificial censoring process, each person-trial will be weighted at each time point by the inverse probability of receiving their assigned treatment strategy, conditional on baseline and time-varying covariates. The pooled logistic model will be fitted to predict the probability of receiving statin therapy at each time point. The last observation carried forward method will be employed to handle missing values in time-varying clinical parameters during the follow-up period. To adjust for potential bias arising from competing events (i.e., death), each person-trial will be additionally adjusted by a time-varying inverse probability weight of not dying. As the treatment strategies in the per-protocol analysis described above are adaptive to the time-varying clinical characteristics (i.e., LDL-C levels and the occurrence of any subtypes of CVDs), we adopted the non-stabilized inverse probability weight, rather than stabilized weight, for estimation of the per-protocol effect after peer review. This change of analytical choice aims to avoid the potential bias introduced by the numerator of stabilized weight. Finally, a pooled logistic model will be fitted to estimate the hazard ratio for outcomes between continuous statin therapy and never using statins during the follow-up period, incorporating the indicators of the assigned treatment strategy, month of follow-up, and baseline covariates, with adjustment for non-stabilized weights as mentioned above. The E-value was calculated to assess the robustness of the estimated results to the potential unmeasured confounding. The absolute risk of the outcome incidence will be estimated by fitting the aforementioned pooled logistic model for causal effect estimation, incorporating product terms between the treatment indicator and time.

**Subgroup analysis:** Subgroup analyses for the risk of overall CVD incidence and all-cause mortality will be conducted based on sex and Charlson Comorbidity Index (<8/≥8) at baseline.

**Sensitivity analysis**: Several sensitivity analyses were conducted. (1) To examine if the length of grace period for the ascertainment of statin discontinuation would have an impact on the results, a sensitivity analysis was conducted by extending this gap from 1 month to 3 months in per-protocol analysis. (2) To evaluate the residual confounding by indication, the patients with familial hypercholesterolemia at baseline were excluded in another sensitivity analysis. (3) An additional sensitivity analysis was conducted regarding the weight truncation at the cut-off of 20. After peer review, we additionally performed the sensitivity analyses below to test the robustness of our results: (4) To test whether the choice of LDL-C cut-off might influence the results, we performed a sensitivity analysis on all patients with T2DM. (5) Regarding the competing event of death, we conducted a sensitivity analysis of estimating the total effects, where death was not considered as a censoring event. (6) As mentioned, a sensitivity analysis was conducted by excluding the participants who had the outcome within the first year of follow-up. (7) As the main analysis was conducted in the matched sample, the estimation better reflects Average Treatment Effect on the Treated (ATT) rather than Average Treatment Effect (ATE). To investigate whether the estimated ATT would differ from the ATE in our study, we additionally performed a sensitivity analysis by including all eligible study participants before matching. (8) Finally, a sensitivity analysis was conducted by removing the exclusion criterion of requiring at least one follow-up visit after baseline. Instead, the person-trials were censored two years after their last recorded visit within the local public healthcare system (i.e., considered them lost to follow-up at this time point) and additionally applied inverse probability weights to account for censoring due to loss to follow-up. (9) For the primary composite outcome, we also analyzed the composite outcome without heart failure for comparison. (10) Finally, for the outcomes of MI and stroke, we performed a sensitivity analysis by excluding the old MI diagnosis (ICD-9 code: 412) or late effects of cerebrovascular disease (ICD-9 code: 438.x) in the case definition for outcome events after baseline.

All analyses will be conducted from September to December 2023 using Stata/MP, version 17.0 (StataCorp LLC). Statistical significance is defined as a two-tailed p-value <0.05.

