**4. STUDY POPULATION**

**Inclusion criteria:** The analysis will include all T2D patients aged ≥60 years with elevated low-density lipoprotein cholesterol (LDL-C) ≥2.6 mmol/L in each calendar month from January 2009 to December 2015. An LDL-C cut-off of 2.6 mmol/L is chosen as this represents the optimal treatment target for T2D patients with no prior history of CVD according to local guidelines (1).

**Exclusion criteria:** Patients who used statins before baseline, or used fibrates or any other lipid-lowering drugs classified under the British National Formulary code 2.12 before baseline will be excluded from the analysis. Individuals with a history of type 1 diabetes, CVDs, cancer, myopathies or liver dysfunction will be excluded. Patients with incomplete data for the study variables at baseline will also be excluded. Eligible patients need to have at least one follow-up visit record after baseline.

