**5. STUDY OUTCOME AND FOLLOW-UP PERIOD**

**Primary outcome:** major CVDs (i.e., a composite outcome of myocardial infarction, heart failure, stroke).

**Secondary outcome:** the three CVD subtypes, all-cause mortality, and muscle-related adverse events (AEs) and liver dysfunction.

After peer review, we also analyzed the composite outcome of major CVD diseases without heart failure as a sensitivity analysis for comparison, and expanded the assessment of muscle-related AEs to include myalgia, myositis, myopathy, and rhabdomyolysis.

Case definition was based on the International Classification of Primary Care, 2nd Edition (ICPC-2) and International Classification of Diseases, 9th Revision, Clinical Modification (ICD-9-CM), or relevant clinical parameters (Appendix I: S3 Table). We excluded patients with pre-existing diagnosed outcomes of interest on or before baseline to ensure the outcome events were restricted to the new incident cases occurring after baseline. The patients with documented old MI diagnosis (ICD-9 code: 412) or late effects of cerebrovascular disease (ICD-9 code: 438.x) on or before baseline were also excluded. For consistency, these two codes were also included in the case definitions for outcome events for MI and stroke. After peer review, we also conducted a sensitivity analysis where these two codes were excluded from the case definition of outcome events for comparison

Patients will be followed up until the outcome of interest, death, or the administrative end of our study (31 December 2018), whichever occurs first. Potential bias of undiagnosed disease might exist for the participants who experienced the outcome incidence within the first year of follow-up. After peer review, we retained these patients in the main analysis and conducted a sensitivity analysis by excluding these patients to test the potential bias (2).

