**7. COVARIATES**

Demographic characteristics (sex and age), clinical parameters plus blood profile (systolic blood pressure, diastolic blood pressure, hemoglobin A1c, LDL-C, high-density lipoprotein cholesterol, total cholesterol, and estimated glomerular filtration rate), comorbidities (hypertension, peripheral vascular disease, atrial fibrillation, chronic obstructive pulmonary disease, renal disease, dementia, obesity, and Charlson Comorbidity Index), drug history within 1 year before baseline (aspirin, insulin, oral antidiabetic drugs, β-blockers, calcium channel blockers, diuretics, and angiotensin-converting enzyme inhibitors), service utilization within the prior 1 year (Specialist Out-Patient Clinic attendance and hospitalization) and lifestyle behavior (smoking status).

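### Baseline calendar month is named only as a matching factor, so sensitivity analysis (7) has no stated control for calendar era and the per-protocol models do not name it

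*Protocol*

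**What the plan says.** Entry and follow-up: Section 4 enrols patients "in each calendar month from January 2009 to December 2015". Section 5 follows everyone to the event, death or "the administrative end of our study (31 December 2018), whichever occurs first".

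Calendar month is named once as an adjustment variable, in the Section 8 main analysis: "The matching factors included the aforementioned covariates and the baseline calendar month". The wording sets it beside the covariates, not among them. The Section 7 list agrees: it runs from demographics to "service utilization within the prior 1 year (Specialist Out-Patient Clinic attendance and hospitalization) and lifestyle behavior (smoking status") and has no calendar variable.

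The models in Section 8:
- ITT outcome model: assigned strategy, "follow-up period (linear and quadratic terms), and the aforementioned covariates at baseline".
- Treatment weights: each person-trial is "weighted at each time point by the inverse probability of receiving their assigned treatment strategy, conditional on baseline and time-varying covariates".
- Death weight: no covariates listed.
- Per-protocol outcome model: strategy, month of follow-up (time since baseline) and baseline covariates.
- Absolute risks: the same model, "incorporating product terms between the treatment indicator and time". No horizon is given.

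Sensitivity analysis (7), meant to show whether the ATT differs from the ATE, reads: "we additionally performed a sensitivity analysis by including all eligible study participants before matching". It names no replacement for the matching.

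**The concern.** By matching on entry month, the plan treats calendar era as a confounder. That is sensible when trials open over seven years in which statin prescribing, coding and recorded CVD rates may all drift.

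Analysis (7) then gives up that control. The Section 7 covariates can still be adjusted through the outcome model. Month is the one matching factor left with nothing stated to handle it. The analysis therefore changes the target population and the era adjustment together. A gap from the main result could be an era effect, and agreement could be two shifts that cancel.

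In the per-protocol analysis the question is narrower. Weights remove bias from artificial censoring only if they condition on the shared causes of censoring and outcome. Calendar time could be one: non-initiators may start statins, or initiators may stop, at rates that move differently over 2009–2018. Balance at baseline does not by itself protect the later risk sets.

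**Working it through.** The protocol gives no event rate, initiation rate or discontinuation rate, so there is no stated figure to reproduce. Two calculations were made.

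**1. Calendar arithmetic (dates from Sections 4 and 5).** January 2009 to December 2015 is 7 × 12 = 84 entry months. Number them m = 0 to 83. Follow-up to December 2018, counting the entry month, is at most 120 − m months: 120 for the first cohort and 37 for the last.

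| Follow-up year | Cohorts contributing something | Cohorts completing it |
|---|---|---|
| 3 | 84/84 (100%) | 84/84 (100%) |
| 5 | 72/84 (86%) | 61/84 (73%) |
| 7 | 48/84 (57%) | 37/84 (44%) |
| 9 | 24/84 (29%) | 13/84 (15%) |
| 10 | 12/84 (14%), all 2009 entrants | 1/84 (1%) |

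**2. Expected hazard ratio when month is left out and the truth is 1.00.** All inputs here are assumptions:
- equal cohort sizes;
- event hazard 3% per year in 2009, the same in both arms, falling by a fraction d per calendar year: h = (0.03/12)(1 − d)^((m+t)/12) at follow-up month t;
- for analysis (7), initiation odds of 0.02/0.98 in January 2009, multiplied by r per year;
- for the per-protocol analysis, equal arms at entry in every month; users censored at 1% per month throughout; non-users at 1% per month, multiplied by r per calendar year;
- no other covariate stands in for era.

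The ratio is stratified by follow-up month only. With D for expected events and Y for persons at risk:

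HR = Σₜ[D₁ₜY₀ₜ/(Y₁ₜ+Y₀ₜ)] ÷ Σₜ[D₀ₜY₁ₜ/(Y₁ₜ+Y₀ₜ)]

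| Analysis | d | r = 1.0 | r = 1.1 | r = 1.2 | r = 1.3 |
|---|---|---|---|---|---|
| (7), month omitted | 2% | 1.000 | 0.994 | 0.988 | 0.983 |
| | 4% | 1.000 | 0.988 | 0.976 | 0.966 |
| | 6% | 1.000 | 0.981 | 0.964 | 0.948 |
| Per-protocol, month omitted | 2% | 1.000 | 0.997 | 0.993 | 0.987 |
| | 4% | 1.000 | 0.995 | 0.986 | 0.975 |
| | 6% | 1.000 | 0.992 | 0.980 | 0.964 |

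Checks on the same model:
- Matched ITT with month balanced: 1.000 throughout.
- Stratifying by entry month as well: 1.000 throughout, for both analyses.
- Per-protocol with censoring rising by 1.2 per year in both arms alike: 1.000 for d of 2%, 4% and 6%.
- Event rates rising 2–6% per year instead: analysis (7) gives 1.006 to 1.048 and per-protocol 1.003 to 1.040, for r from 1.1 to 1.3.

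The last column is demanding. Over the 83 months between first and last entry, r = 1.3 multiplies initiation odds by 1.3^(83/12) ≈ 6.1; r = 1.2 gives about 3.5 and r = 1.1 about 1.9. By the last month of follow-up, r = 1.3 takes non-user censoring from 1% to 1.3^(119/12) ≈ 13.5% per month.

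**The case against.** The strongest reply is that omission is inferred from silence for most of the models. The weights and the per-protocol outcome model refer to baseline covariates without tying the phrase to the Section 7 list. Entry month is a baseline variable already used for matching, so the phrase could include it. The death weight lists nothing. Analysis (7) says who is included, not how they are adjusted. A statistical analysis plan that is not shown may list the terms. This stands in part: only the ITT model, which points back to the listed covariates, clearly omits month. The rest should be described as not named. But the protocol sets out its model terms itself and names month separately when it wants it, so the reader cannot assume that it is there.

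It is also fair to say that (7) is one of several robustness checks added after peer review, that every trend above is assumed, and that the shifts are small.

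A reader might infer more than the document supports:
- *That any secular trend biases the per-protocol hazard ratio once matched pairs are broken.* The models do not use pair membership, and a trend common to both arms cancels within follow-up months. Bias needs arm-differential, era-dependent censoring together with an outcome trend.
- *That the main ITT hazard ratio is biased.* It is not, provided that matching balances month. Propensity score matching does not guarantee exact pairing on month, so that balance should be checked.
- *That thin late follow-up comes from omitting month.* It comes from staggered entry and a single end date. Adding month supplies no late data.

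**Conclusion.** The point holds in a limited form. It is clearest for analysis (7), which as written has no control for calendar era and so cannot isolate ATT from ATE. For the per-protocol analysis it is a conditional risk: the models do not name calendar time, and bias follows only if censoring and outcome both trend in the way described.

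The size is a few percent on the hazard ratio, at most about 5% in (7) and about 4% per-protocol in the ranges tried. The direction depends on whether recorded event rates fall or rise. With falling event rates and rising statin uptake, both analyses move towards apparent benefit and could seem to corroborate each other. These figures rest wholly on assumed trends and on no other covariate absorbing era.

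The absolute-risk matter is a separate reporting point. Every entry month covers only about 36 months, and year 10 rests on 2009 entrants alone. The protocol states no late horizon, so it cannot be said to present late risks as applying to the whole cohort.

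**What to change.** 1. Add baseline calendar month, for example as a spline, to the outcome model of sensitivity analysis (7), and say so in its description.
2. Add it to the per-protocol treatment-weight, death-weight and outcome models. Together with month of follow-up it determines calendar time, so the weight models should contain both.
3. Add it to the matched ITT model as well. This is harmless and keeps the models consistent, though it is not needed for validity if month is balanced.
4. State the horizon for absolute risks. Label any estimate beyond about 36 months with the entry cohorts that support it.

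If month was already in these models, one sentence listing it settles items 1 to 3.

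Cost: a few model terms from a variable already held, and re-running the models. No new data are needed.

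### Monthly person-trials are matched and adjusted without time since first eligibility or diabetes duration, which leaves avoidable residual confounding of unproven direction

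*Protocol*

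**What the plan says.** Protocol section 4 applies the inclusion criteria "in each calendar month from January 2009 to December 2015". Section 8 uses propensity score matching to "emulate the randomization of the eligible person-trials at baseline", so the unit is the person-trial and not the patient. Re-entry is implied by these two statements and is not spelled out.

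The exclusion in section 4 removes "Patients who used statins before baseline, or used fibrates or any other lipid-lowering drugs" but sets no limit on how long someone may have been eligible and untreated.

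Section 8 states that "initiators and non-initiators will be matched in a 1:1 ratio within each age group", and then: "The matching factors included the aforementioned covariates and the baseline calendar month". The covariates are those of section 7. The list opens with "Demographic characteristics (sex and age), clinical parameters plus blood profile" and goes on to comorbidities, "drug history within 1 year before baseline (aspirin, insulin, oral antidiabetic drugs" and other agents), "service utilization within the prior 1 year", and smoking. It has no diabetes duration, no time since first eligibility and no count of earlier person-trials. The ITT outcome model adjusts for the same covariates. None of sensitivity analyses (1) to (10) adds such a variable or restricts the analysis to first eligible months.

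**The concern.** In any month the non-initiators include everyone who was eligible earlier and has still not started. If people differ in how readily they start a statin, through preference, prescriber or frailty that the covariates do not capture, the fast starters leave the pool first. Initiation then falls with time eligible even if each person's own rate is constant. A newly eligible initiator can be paired with a control who has been passed over for years, and the two need not share the same prognosis.

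Baseline calendar month does not deal with this, because patients become eligible at different times: two people in the same month can have very different waiting times. One-year look-backs for drugs and service use do not record it either. Diabetes duration is a separate variable, also absent, and a plausible confounder in its own right.

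At stake is a distortion of the ITT hazard ratio, perhaps differing by age group, that the analysis cannot show because the balance of these variables is never examined.

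**Working it through.** The protocol gives no initiation rate, event rate or bias figure, so there is nothing of its own to reproduce. Every rate below is an assumption. The only design input taken from the document is the schedule: 7 years × 12 = 84 monthly baselines. Diabetes duration was not modelled.

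**Step 1. Does re-entry alone unbalance time eligible?** Assumptions: constant monthly inflow, a pool with up to 60 months of prior eligibility at the start, and initiators compared with same-month non-initiators. Let g be control minus initiator mean time eligible, in years, and r the hazard ratio per extra year eligible and untreated. With no true statin effect, the spurious HR is r^(−g).

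| Monthly initiation by time eligible | Initiators (months) | Controls (months) | g (years) | HR, r = 1.04 | HR, r = 0.97 |
|---|---|---|---|---|---|
| Constant 2% | 33.9 | 33.9 | 0 | 1.00 | 1.00 |
| Falling 5% to 1% | 25.4 | 39.5 | 1.17 | 0.955 | 1.036 |
| Falling 10% to 0.5% | 17.8 | 44.8 | 2.25 | 0.916 | 1.071 |
| Rising 0.5% to 3% | 39.1 | 31.0 | −0.67 | 1.027 | 0.980 |

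For example, (44.8 − 17.8)/12 = 2.25 and 1.04^(−2.25) = 0.916. Re-entry by itself creates no gap. A gap needs initiation to change with time eligible, and the sign of the bias depends on both g and r. The range is about 0.92 to 1.07.

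**Step 2. What would adjustment recover if the real driver is an unmeasured trait?** Assumptions: two equal-sized patient types, fast and slow starters; 84 monthly trials; 60-month follow-up; outcome rate 0.2% a month in fast starters; no true effect; nobody already eligible at the start. The initiators' event rate is divided by the control rate standardised (a) by calendar month and (b) by calendar month and months since first eligible. Share of log bias removed = 1 − ln(HR b)/ln(HR a).

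| Initiation, fast vs slow | Outcome rate ratio, slow vs fast | HR (a) | HR (b) | Share removed |
|---|---|---|---|---|
| 20% vs 0.5% | 1.5 | 0.748 | 0.787 | 1 − 0.240/0.290 ≈ 17-18% |
| 5% vs 0.5% | 1.5 | 0.811 | 0.822 | 1 − 0.196/0.209 ≈ 6% |
| 20% vs 0.5% | 0.8 | 1.175 | 1.137 | 1 − 0.128/0.161 ≈ 20-21% |
| 5% vs 0.5% | 0.8 | 1.119 | 1.109 | 1 − 0.103/0.112 ≈ 8% |

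In the first row initiators average 6.9 months eligible and their calendar-month controls 19.3. Across all scenarios run, including 0-60% of patients already eligible at the start, the share removed was about 2-21%. Adjustment moved the HR towards 1 in each of them, whichever side it started on.

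**The case against.** A reader might infer three stronger things, and the documents support none of them.

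- **That monthly re-entry necessarily pairs recent starters with long-untreated controls.** It does not. In each month both arms come from the same eligible pool, and under constant initiation the gap is zero. The figure of 84 describes the candidate pool; 1:1 matching with calendar month among the factors means those person-trials do not all enter the analysis.
- **That the ITT result leans towards benefit.** The protocol says nothing that fixes the sign. Sections 4 and 5 remove patients with prior CVD, cancer, liver dysfunction or other outcome diagnoses, so long-eligible controls are event-free survivors. Some may be untreated because they were judged low risk. Both push towards harm.
- **That an HR near 0.75 measures this omission.** It measures an assumed unmeasured trait with a 40-fold difference in initiation (20% vs 0.5%). Leaving out time eligible accounts for only a small part of it.

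The plan also has partial protection. HbA1c, eGFR, renal disease, insulin, oral antidiabetic drugs and the Charlson index are partial proxies for duration and frailty. Sensitivity analysis (6), which drops first-year outcomes, bears on short life expectancy. The E-value and the 60-74 benchmark are general checks: they do not correct this imbalance, and agreement at 60-74 cannot rule out a larger problem at older ages.

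Finally, first eligibility depends partly on when LDL-C was tested, and the protocol states neither the look-back before 2009 nor whether diabetes onset is recorded.

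What remains is that two plausible confounders are missing from a stated matching list and a stated outcome model. A falling initiation rate is a reasonable expectation when starting propensity varies unmeasured, though not a certainty.

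**Conclusion.** The point holds as an omission in the stated specification: a sequential monthly design whose matching factors and ITT model carry neither time since first eligible nor diabetes duration. It leaves possible residual confounding of unproven direction. The size cannot be computed from the protocol. Under the assumed rates, the part due to time eligible itself lies between about 0.92 and 1.07 on the HR scale. Where an unmeasured trait is the driver, adjustment recovers about 2-21% of the log bias and the rest stays. This is a low-cost improvement and does not invalidate the main analysis. It rests on re-entry being intended and on initiation varying with time eligible after conditioning on the section 7 covariates.

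**What to change.** For each person-trial, derive months since the first eligible month and, where recorded, months since the first T2D record. Enter both as flexible terms in the propensity score, the outcome models and the weight models. Exact bands are not required. Add an indicator for patients already eligible in January 2009, whose earlier waiting time is not observed within the window. Report the balance of both variables after matching, by age group.

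Time since first eligible comes from the monthly eligibility data that the design already needs; diabetes duration depends on what the records hold. The cost is one or two derived variables and possibly a few unmatched initiators at ≥85 years, a loss that flexible terms limit compared with narrow bands. The report should say that this adjustment does not remove most bias from unmeasured frailty.

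### Sensitivity analysis (7) is meant to compare ATT with ATE, but for the ITT hazard ratio dropping the matching changes the sample and, if monthly initiation is low, hardly changes the estimand

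*Protocol*

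**What the plan says.** The main analysis (Protocol, section 8) is done in a matched sample: "initiators and non-initiators will be matched in a 1:1 ratio within each age group". Item (7) of the sensitivity analyses accepts that such an estimate lies nearer the ATT than the ATE. It gives its purpose as "To investigate whether the estimated ATT would differ from the ATE in our study", and the one change it names is "we additionally performed a sensitivity analysis by including all eligible study participants before matching". It does not restate an outcome model.

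The models it would inherit are in the main-analysis paragraph:

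- **ITT.** A single pooled logistic regression yields the hazard ratio. Its terms are listed as "including the indicators of the assigned strategy (statin initiation at baseline), follow-up period (linear and quadratic terms), and the aforementioned covariates at baseline". No baseline treatment weights and no treatment-by-covariate products are mentioned.
- **Absolute risks.** The same models, "incorporating product terms between the treatment indicator and time". The products are with time only, not with covariates.
- **Per-protocol.** "each person-trial will be weighted at each time point by the inverse probability of receiving their assigned treatment strategy". These weights are introduced to deal with artificial censoring. Whether they also cover the decision at baseline is not said.

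Section 4 assesses eligibility in each calendar month from January 2009 to December 2015, which is 7 x 12 = 84 monthly trials. No initiation rate is given anywhere.

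**The concern.** Which patients are in the data set and which population the estimate refers to are separate matters. Adding the unmatched non-initiators brings in every eligible person-trial, but a model with one common treatment coefficient does not then average the effect over all eligible person-trials. It learns about the treatment effect mainly where initiators are found. If few patients start a statin in any one month, that is the covariate distribution the matched sample already has.

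Analysis (7) could then agree closely with the main result even when ATT and ATE differ. A reader could take that agreement as support for extending the result to eligible patients who are seldom started on a statin. This bears on the objective in section 2, which concerns patients aged 75-84 and 85 or over without limiting it to those likely to be treated.

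**Working it through.** **No plan figure to reproduce.** The Protocol gives no initiation rate, event count or expected hazard ratio. All numerical inputs below are assumptions chosen to show the mechanism.

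**Formula.** With effects that differ between strata x and a single fitted treatment coefficient, the hazard ratio is approximately

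HR = sum of w(x) HR(x) / sum of w(x), with w(x) = f(x) h(x) g(x).

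Here f is the stratum's share of eligible person-trials, h its relative baseline event rate and e its monthly initiation probability. The factor g depends on the analysis:

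- matched 1:1: g = e
- all person-trials, unweighted: g = e(1-e)
- all person-trials weighted to the full eligible population (ATE): g = 1

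When e is small, e(1-e) is close to e.

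**Main illustration.** Stratum A has f = 0.3, e = 0.04, HR 0.65 and h = 1.5. Stratum B has f = 0.7, e = 0.01, HR 1.0 and h = 1.

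- Matched: weights 0.3 x 1.5 x 0.04 = 0.0180 and 0.7 x 0.01 = 0.0070. HR = (0.0180 x 0.65 + 0.0070) / 0.0250 = 0.748.
- Unmatched, unweighted: weights 0.0180 x 0.96 = 0.01728 and 0.0070 x 0.99 = 0.00693. HR = (0.01728 x 0.65 + 0.00693) / 0.02421 = 0.750.
- ATE: weights 0.45 and 0.70. HR = (0.45 x 0.65 + 0.70) / 1.15 = 0.863.

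Logistic regressions on the expected cell counts (baseline monthly risk 0.3%) give the same three values. Fitted results for this and other settings:

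| Setting (assumed) | Matched | Unmatched, unweighted | ATE |
|---|---|---|---|
| Main illustration, initiation 4% and 1% | 0.748 | 0.750 | 0.863 |
| Same, initiation 10% and 2% | 0.733 | 0.737 | 0.863 |
| Same, initiation 30% and 10% | 0.770 | 0.786 | 0.863 |
| Milder: 50% with HR 0.70, initiation 2%; 50% with HR 0.95, initiation 1% | 0.763 | 0.763 | 0.800 |
| Main illustration with the two HRs exchanged | 0.902 | 0.900 | 0.787 |

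**Second set-up, with follow-up time in the model.** Two equal strata, initiation three times as likely in one, HR 0.6 in that stratum and 0.9 in the other, monthly hazard 0.003, 60 months, linear and quadratic time. The matched HR is 0.674 and the ATE 0.748. The unmatched, unweighted HR by mean monthly initiation is:

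| 1% | 5% | 10% | 20% | 30% | 45% |
|---|---|---|---|---|---|
| 0.673 | 0.675 | 0.678 | 0.684 | 0.694 | 0.721 |

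Up to about 10% per month the unmatched HR stays within 0.004 of the matched one (0.678 - 0.674), while the ATE is about 0.075 away. The similarity fades above that.

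**Absolute risks at 1% initiation, same set-up.** Standardised to all participants, the unweighted model gives a 60-month risk difference of -0.051 (true ATT -0.051, true ATE -0.039). If the baseline hazard is twice as high in the high-initiation stratum (0.004 against 0.002), it gives -0.055, between the true ATT of -0.062 and the true ATE of -0.045.

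**Effect of the fix.** With baseline inverse-probability weights, the second set-up returns HR 0.748 at every initiation rate tried and a risk difference of -0.039.

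**The case against.** The strongest reply is that item (7) states a sample and not a model. That it is unweighted is inferred from the ITT paragraph, and the detailed estimator may stand in an analysis plan that is not at hand. The inference is nevertheless the natural one, because the Protocol names weights where it uses them: for the per-protocol analysis, and in item (8) for loss to follow-up. Item (7) also sets out both a purpose and a method, and for the ITT hazard ratio that method does not deliver the purpose. This is more than absent detail.

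Four further objections stand and limit the point:

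- **Low initiation is assumed.** Monthly trials make it plausible, but the patients are untreated with LDL-C at or above the treatment target, and no rate is reported.
- **The per-protocol analysis is weighted.** If its weights include the baseline decision, running it on all eligible person-trials does target the ATE. If they begin after baseline, the same problem arises. The text does not settle which.
- **Heterogeneity is needed.** Without effect variation along predictors of initiation there is essentially no gap to find. The main illustration assumes strong variation, and the milder case leaves 0.763 against 0.800. The Protocol also looks at heterogeneity directly, by age group, sex and Charlson index.
- **Absolute risks are not wholly insensitive,** as the unequal-hazard result shows.

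A reader might infer that analysis (7) cannot detect any difference between ATT and ATE, or that it must agree with the matched result. The documents do not support that, because they fix neither the model for (7) nor the initiation rate, and they also plan absolute risks. Nor do they say that agreement will be presented as proof of generalisability; the stated aim is only to investigate.

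**Conclusion.** The point holds for the ITT hazard ratio, provided that item (7) uses the ITT model of section 8 and that monthly initiation is low. In the examples, low means up to about 10%. Under those conditions, agreement between (7) and the main analysis is weak evidence that ATT equals ATE: the unmatched estimate moves by 0.004 or less from the matched one, while the ATE differs by 0.037 (0.800 - 0.763) in the mildest example and 0.130 (0.863 - 0.733) in the strongest. The direction is not fixed, since exchanging the stratum effects reverses it.

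The label ATT is itself approximate for a common-coefficient hazard ratio, because that average also depends on event rates. For the per-protocol effect the question is open. The primary estimate is not affected. The change is worth making because, as described, this check may not answer the question it was added for.

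**What to change.** State the estimator for (7), and choose one that targets all eligible person-trials. Either:

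- weight each eligible person-trial by the inverse probability of the baseline strategy received, 1/e for initiators and 1/(1-e) for non-initiators, with truncation at stated percentiles; or
- fit the outcome model with treatment-by-covariate products and standardise the risks over all eligible person-trials.

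For the per-protocol version of (7), say that the weights include the baseline decision. Compare the result with the matched estimate on the same scale, for both hazard ratio and risk difference. Report the monthly initiation rate by age group, so that readers can judge how far the two targets could part.

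Truncation needs care. At initiation of 4% and 1% the initiator weights are 1/0.04 = 25 and 1/0.01 = 100. A fixed cut-off of 20, the value named in sensitivity analysis (3), would set both to 20 and undo most of the reweighting.

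The cost is one extra step, using a propensity score of the kind already needed for matching, and a wider confidence interval than the unweighted model gives. If this is not wanted, keep (7) as a check on the matching step and do not describe it as an ATE comparison.
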